**A randomised controlled trial of teprenone in terms of preventing worsening of COVID-19 infections**

# １．Study title

　A randomised controlled trial of teprenone in terms of preventing worsening of COVID-19 infections

# ３．Background, objective and significance of the study

**Background**

COVID-19 caused by SARS-CoV-2 has become a global pandemic with an exponential increase in the number of infections and deaths. 26% of patients hospitalized with COVID-19 are considered severe cases requiring intensive care unit admission1. Severe acute Severe acute respiratory infection (SARI) can be complicated by acute respiratory distress syndrome (ARDS), sepsis and septic shock, and multiple organ failure (Lancet Respir Med. 2020. Epub 2020/02/28). It is difficult to identify patients with COVID-19 who are expected to progress to SARI, and there is no established treatment to delay the progression to SARI. Although steroids have been administered to severe cases of SARI, findings from SARS and MERS suggest that steroids delay viral elimination and do not contribute to improved survival (PLoS Med 2006; 3: e343. Am J Respir Crit Care Med 2018; 197: 757 ); TNF-α and Th1/Th2 cytokines are elevated in severe cases of COVID-19 (Lancet 2020; 395: 497), suggesting that excessive stress, mainly cytokines, induces SAPK/JNK, resulting in cytotoxicity and leading to severe COVID-19 pneumonia Heat Shock Protein

　Heat shock proteins (HSPs) are a family of proteins that are up-regulated when cells are exposed to heat or other stress conditions and protect cells. Among them, HSP70 protects cells from damage caused by TNF-alpha (J Immunol 1993; 151: 4286) and reactive oxygen species (ROS) (FEBS Lett 1996: 391; 185).

It is known from preclinical data that teprenone (セルベックス®) has a cytoprotective effect by inducing HSP. In guinea pig gastric mucosal cells, teprenone has been shown to induce HSP60, 70, and 90 and to have cytoprotective effects2, and in rat myocardium it has been shown to protect against cell damage caused by ischemia3. In a mouse model of interstitial pneumonia, oral teprenone induced HSP-70 in the lung, reduced macrophage inflammatory protein-2 (MIP-2) and inflammatory cell infiltration, and inhibited lung fibrosis.4 In addition, gefitinib is known to cause drug-induced pneumonitis as an important adverse event.5 In addition, gefitinib is known to cause drug-induced pneumonitis,5 and administration of gefitinib to a bleomycin interstitial pneumonia mouse model decreased HSP-70 expression in lung tissue and exacerbated interstitial pneumonia.6 On the other hand, administration of teprenone restored HSP-70 expression, suppressed exacerbation of interstitial pneumonia, and prevented fibrosis.6 6 Furthermore, in a model of radiation pneumonitis induced by thoracic irradiation in C57BL/6 mice, teprenone administration inhibited lung fibrosis by suppressing HSP-70 induction and epithelial-mesenchymal transition.7 Thus, teprenone has been reported to have lung protective effects in various lung injury models. In vitro, 1uM of teprenone induces HSP70 in (gastric mucosa) cells and has cytoprotective effects. In humans, a single 150mg dose of teprenone has a blood concentration Cmax of 3-7uM. There is no data on the blood concentration of teprenone 50mg x 3 times (standard dose), but considering the above blood concentration and the concentration at which it has cellular effects, it is possible that the standard dose will be sufficient to produce an effect.

Viral pneumonia is caused by not only direct damage caused by viral proliferation in infected cells but also damage to non-infected cells caused by ROS from infiltrating neutrophils and macrophages. In addition to cytokines, control of cytotoxicity caused by ROS such as superoxide and NO is thought to be important in reducing the severity of the disease. Thioredoxin-1 (TRX-1) is a protective protein induced under stress conditions, and is an antioxidant enzyme with an SH group that has redox activity. it has cytoprotective effects against ROS, inhibits migration and adhesion of neutrophils and macrophages, suppresses AP-1 and NF-b, and inhibits complement activation. Yahsiro et al. demonstrated in an animal model that TRX-1 treatment reduced cytokines, neutrophil infiltration, and tissue damage in influenza pneumonia (Crit Care 2009; 61:303). In addition to HSP70, GGA has the ability to induce this TRX-1.

Based on the above basic findings, it is suggested that teprenone may reduce the severity of COVID-19 pneumonia. Other non-steroidal drugs currently in development include the anti-influenza drug favipiravir, the anti-HIV drug lopinavir-ritonavir, as well as Nafamostat mesylate and Camostat mesylate and Camostat, which inhibit viral receptors. All of these therapies target viruses and have different mechanisms of action from the cytoprotective action of teprenone, so they are expected to be effective in combination.

**Objective**

To determine whether teprenone is effective in reducing the severity of disease in patients with COVID-19.

**Significance**

If we can prevent COVD-19 pneumonia from becoming severe, we can not only reduce the number of potentially fatal cases, but also reduce the burden on the medical system by decreasing the number of ventilator and ECMO requirements, which will help prevent medical collapse.

2. Prepare a list of research subject identification codes (correspondence table) to be kept by the principal investigator, and describe the date of obtaining consent and the items necessary to correspond the research subject to the research subject identification code. The list shall include the registration number and allocation number issued by INDICE Cloud.
3. Record the research subject identification code and other information in the case list and case report form (CRF).
4. Treatment with or without teprenone based on the patient's research subject identification code.
5. If any withdrawal of consent, discontinuation, dropout, or deviation from the protocol occurs during the research period, it should be promptly reported to the principal investigator and the principal investigator (research secretariat). Upon receiving the report, the principal investigator will decide on an appropriate policy in consultation with the submitting physician and others, giving due consideration to the safety of the patient and the ethics of the research, and record the discussion in the medical record.
6. In case of incompleteness in registration or allocation, or inquiries regarding eligibility determination, the research secretariat will be contacted and the principal investigator will respond.

【Setting of the minimization method】

Age (over/under 70 years), gender, and comorbidities (hypertension, diabetes, cardiovascular disease, chronic lung disease, and cancer) will be used as allocation factors.

If the difference between the treatment group and the non-treatment group is more than 3, forced allocation to the lesser group will be performed, and if the difference is less than 3, random allocation will be performed.

（８）What to do after the research is completed

　　After the completion of this research, the principal investigator will provide the research subjects with medical care that he or she deems most appropriate, including the results obtained from this research.

# ５．Observation and test items

（１）Clinical characteristics of the enrolled patients

　　Age, gender, current medical history, comorbidities, previous medical history, smoking history, height, weight, and Concomitant medication/concomitant treatment

（２）Inspection Items

Blood count (WBC, white blood cell image)、

Biochemical test（AST、ALT、LDH、TP、Na、K、Cl、BUN、CRP、PCT、KL-6）

Chest X-ray、chest CT、SpO_2_

Biomarkers (using residual serum from routine blood collection) Comprehensive cytokine analysis using multiplex system, Hydropeoxides, TRX-1 and HMGB-1, HSP70, S100A8/A9

（３）Check for adverse events and side effects

The details of adverse events, time of onset and resolution, degree, treatment, outcome, severity assessment, and relationship to teprenone medication should be described in the CRF. If necessary, follow-up will be conducted until the time when isolation, including home isolation, is lifted.

| Item/period of inspection/investigation | Screening  (within 7 days before registration)Scre | Registration | Intervrnyion | | | | | follow up | | at the timing of intubation |
| --- | --- | --- | --- | --- | --- | --- | --- | --- | --- | --- |
|  |  |  | Day1 | Day3 | Day5 | Day7 | Day10 | Day14 | Day21 |  |
| Eligibility verification and registration |  | ● |  |  |  |  |  |  |  |  |
| COVID-19 PCR | ○ |  |  |  |  |  |  |  |  |  |
| clinical examination |  |  |  |  |  |  |  |  |  |  |
| blood count and biochemistry | ○ |  | ● |  | ▲ |  | ▲ | ▲ | ▲ | ▲ |
| KL-6・ | △ |  |  |  |  |  |  |  |  |  |
| procalcitonin |  |  |  |  |  |  |  |  |  |  |
| temprature | ○ | ● | ● | ● | ● | ● | ● | ▲ | ▲ | ● |
| dose of oxygen | 〇 |  | ● | ● | ● | ● | ● | ▲ | ▲ | ● |
| SpO2 | ○ |  | ● | ● | ● | ● | ● | ▲ | ▲ | ● |
| biomarker |  |  |  |  |  |  |  |  |  |  |
| Serum storage for biomarkersseru |  |  | ▲ |  | ▲ |  | ▲ |  |  |  |
| effect determination |  |  |  |  |  |  |  |  |  |  |
| chest X-ray | △ |  |  | ▲ |  |  | ▲ |  | ▲ | ▲ |
| chest CT | △ |  |  |  |  |  | ▲ |  | ▲ | ▲ |
| toxicity assessment |  |  |  |  |  |  |  |  |  |  |
| Subjective and subjective symptoms |  |  | ● | ● | ● | ● | ● | ● | ▲ | ▲ |

**【Schedule】**

**Patients who are discharged early will be observed within the observable period and do not need to come to**

**the hospital only for this study.**

△・▲ Not required, but recommended to be done whenever possible　　〇・△before registration、●・▲after registration

# ６．Evaluation Items

（１）Primary endpoint

　　Intubation rate

Indications for considering endotracheal intubation：

１．PaO2 less than 60 Torr under adequate oxygen therapy

２．Acute respiratory acidosis

３．Decreased level of consciousness, odd breathing, dyspnea

（２）Secondary endpoint

　　①mortality

　　②time to fever resolution

Fever：equal to or more than 37.5℃

Alleviation of fever：To be below 37.5℃ for more than 24 hours without the use of antipyretics

　　③dose of oxygen

　　④radiographic change with CT

⑤improvement of blood test

⑥severity

⑦time to discharge

⑧time to resolution of symptoms

　　⑨adverse events（CTCAE* version 5.0）*: Common Terminology Criteria for Adverse Events

# ７．Target number of the included patients and rationale for setting

　　【Target number of the included patients 】100

【Rationale for the target number】

We calculated the probability of verifying a significant difference in the primary endpoint between the groups (statistical power) in this number of cases. When the endotracheal intubation rate in the non-treated group was set at 22% and that in the treated group at 10%, and α = 0.1 (one-sided), the statistical power was 0.6406.

The rate of endotracheal intubation in the non-treated group is based on the National Institute of Infectious Diseases (Japan), and according to information published on the Web, of 287 cases of COVID-19 infection as of March 9, 2020, information on invasive ventilation was available for 133 cases. Of these, 29 (22%) were reported to have undergone endotracheal intubation.（<https://bit.ly/3eiiMhg>）。

# ８．Data aggregation and statistical analysis methods

All entries (e.g., CRF entries, database creation, entries in related reports, etc.) will be made by either the principal investigator, the principal investigator, or a research collaborator authorized by the principal investigator. The principal investigator will ensure the accuracy, completeness, and timeliness of the data and all other required reports. Data reported in CRFs that are derived from source documents (e.g., patient medical records) must be consistent with those source documents. In the event of any discrepancies, the rationale for the discrepancy should be provided in writing, signed and dated by the principal investigator, and kept in the research subject's file. All data must be derived from the original source.

Data on patients who drop out due to withdrawal of consent during the course of the study will not be used. For patients who drop out for other reasons, the available data up to the time of dropout will be used. Extreme outliers in continuous variables will not be excluded from the statistical analysis. If it is considered necessary to change the original statistical analysis plan (see below), the principal investigator and sub-investigators will consult with each other before changing the statistical analysis plan. No interim analysis will be conducted.

（１）Population for analysis

The population for the analysis of efficacy will be defined as all patients who have been assigned by the minimization method and have not withdrawn their consent.

The safety analysis population will be defined as all patients who have received at least one dose of the assigned treatment. In other words, patients in the teprenone-treated group will be those who have received at least one dose of teprenone, and patients in the non-treated group will be those who have not received any dose of teprenone during their participation in the study.

（２）Analysis method

The obtained data is entered into a dedicated database for tabulation and analysis.

【Main analysis and decision criteria】

For the primary endpoint of endotracheal intubation rate, if the null hypothesis "the rate of endotracheal intubation in the non-treated group is equal to the rate of endotracheal intubation in the treated group" is rejected, it was judged to be effective. If not, it is considered invalid from a clinical medical standpoint. The significance level for the entire study is set at 10% on one side. No adjustment for multiplicity will be made.

【Efficacy analysis 】

The analysis of efficacy is based on the treatment assigned to the patients by the minimization method according to the intention-to-treat (ITT) principle. An ITT analysis is defined as a method of analysis based on the assignment of a treatment group to a treatment or non-treatment group that is determined prior to the initiation of the intervention, rather than on the actual intervention performed. For example, patients who are assigned to the treatment group but never receive treatment for some reason are treated as the treatment group.

Analysis of the primary endpoint (endotracheal intubation rate)

1. Method of main analysis

Based on the observed endotracheal intubation rate, a binomial test will be performed for the null hypothesis that "the rate of endotracheal intubation in the non-treated group is equal to the rate of endotracheal intubation in the treated group. The competing hypothesis will be "the tracheal intubation rate of the treated group is less than that of the non-treated group". If the null hypothesis is rejected, the test is considered valid; if not, the test is considered clinically invalid. The risk ratio is calculated by dividing the risk of tracheal intubation in the treated group by the risk of tracheal intubation in the non-treated group. The exact 90% confidence interval based on the binomial distribution will be used to estimate the interval of the risk ratio.

1. Subgroup analysis will be conducted based on the factors described below.

＜Factors for which subgroup analysis is planned＞

Under 70 years old / Over 70 years old ・ Male / Female ・ Smoking history/No smoking history

Analysis of secondary endpoints (mortality)

The analysis will be performed in the same way as for the primary endpoint.

【Safety analysis】

Calculate the number and percentage of patients in the CTCAE version 5.0 Grade 1 to Grade 5 groups in the treated and non-treated groups, respectively.

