# １１．Background and scientific rationale for the study (rationale and validity of the study)

Background

As described previously (3. Background, objective and significance of the study), we are in the midst of a global pandemic of COVID-19, and the development of treatment to prevent severe disease as well as the development of antiviral drugs is an urgent issue. Treatment for prevention of severe disease is a therapeutic strategy that should be used in combination with antiviral therapy to be developed in the future. Therefore, a treatment method with as few adverse events as possible and easy access to therapeutic agents would be ideal.

Rationale and validity of the study

The purpose of this study was to investigate the effect of teprenone on the prevention of aggravation of COVID-19. We believe that a randomized controlled trial with and without teprenone is a reasonable study design to achieve the purpose of this study.

Fever is one of the major symptoms of COVID-19, and the time to fever resolution is a reasonable primary endpoint.

A network of five major public hospitals, including Okayama University Hospital (Okayama Medical Cooperation Promotion Council), a clinical trial network in the Chugoku-Shikoku region, and designated medical institutions for Class II infectious diseases in the Kanto and Kinki regions are planned as the research system, and an appropriate system is in place to register the planned 100 cases.

Although it is difficult to accurately predict the number of COVID-19 cases, we believe that the planned number of cases can be enrolled within the study period, because more than 2,600 cases have been observed in Japan as of April 3, 2020, and the number of cases is rapidly increasing.

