（５）Discontinuation criteria for individual research subjects

【What to do when the study is discontinued】

When the principal investigator or sub-investigator judges that it is impossible to continue the research on an individual research subject for any of the reasons listed below, the research on that research subject will be discontinued. In such cases, the reason for discontinuation will be explained to the research subjects as necessary. Regarding the treatment of the research subjects after the discontinuation, we will respond in good faith so as not to disadvantage the research subjects.

【Discontinuance criteria】

①If the research subject declines to participate in the research or withdraws his/her consent

②If the continuation of this study is judged to be difficult due to the progression of COVID-19 or its complications.

③Intolerable adverse events

④In case the study itself is discontinued

⑤If, for any other reason, the principal investigator or sub-investigator decides that it is appropriate to discontinue the research（In this case, record the reason for the discontinuation.）

【What to do when study treatment is discontinued】

If the principal investigator or sub-investigator determines that it is not possible to continue the study treatment for an individual research subject for any of the reasons listed above, the investigator or sub-investigator will discontinue the study treatment for that research subject. In this case, the reason for discontinuation will be explained to the research subject as necessary. In addition, the treatment of the research subject after discontinuation will be handled in good faith so as not to disadvantage the research subject.

Of the patients who discontinued study treatment, those who received the study drug will continue to be observed for safety evaluation.

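### COVID-19 progression may end a patient's research follow-up and data are then used only to dropout, so an ordinary analysis of the three recovery times would be informatively censored

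*Protocol*

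**What the plan says.** Section 6 (2) lists three times to a good outcome among the secondary endpoints: fever resolution, discharge and symptom resolution. The schedule in section 5 ends at Day 21.

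Section 14 (5) gives the discontinuance criteria. The second is that continuing is judged difficult because COVID-19 or its complications have progressed. The consequence reaches beyond the drug: "for any of the reasons listed below, the research on that research subject will be discontinued". For those who stop treatment, the same section adds: "Of the patients who discontinued study treatment, those who received the study drug will continue to be observed for safety evaluation".

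Section 8 has two rules for patients who leave. For consent withdrawal: "Data on patients who drop out due to withdrawal of consent during the course of the study will not be used". For everyone else: "For patients who drop out for other reasons, the available data up to the time of dropout will be used". A patient discontinued for progression who has not withdrawn consent can only fall under the second.

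Section 8 also states: "The analysis of efficacy is based on the treatment assigned to the patients by the minimization method according to the intention-to-treat (ITT) principle". It gives an analysis method for intubation and for mortality, and none for the three recovery times.

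**The concern.** Progression is a poor-prognosis event, and it is the event the drug is meant to prevent. If a patient's time data stop there, a standard Kaplan-Meier or log-rank analysis treats that patient as someone who would have recovered at the same rate as patients still doing well. This overstates recovery, and does so more in the arm with more progression. On the plan's own rates that is the control arm.

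At stake is the part of a treatment benefit that comes from keeping patients from progressing, which is the trial's stated objective. The gap in follow-up is also uneven. Observation after stopping treatment is promised only to drug recipients and only for safety, so controls are not covered. The decision to discontinue is made in an open-label trial by someone who knows the arm.

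**Working it through.** **1. The plan's own figure.** Section 7 gives 22% vs 10% intubation, one-sided α = 0.1, 100 patients and power 0.6406. I take 50 per arm, inferred from the minimization rule in section 4 (7). With pooled rate 0.16:

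Power = Φ{[0.12 − 1.2816 × √(2 × 0.16 × 0.84/50)] / √(0.22 × 0.78/50 + 0.10 × 0.90/50)} = Φ{(0.12 − 0.0940)/0.0723} = Φ(0.360) = 0.6406.

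The figure reproduces, so I use 22% and 10% as the progression rates below. Intubation stands in for progression because the protocol gives no dropout rate.

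**2. How the rules combine.** Section 14 (5) can end the research on a progressing patient. Section 8 then uses that patient's data to dropout only. The ITT paragraph fixes the arm in which a patient is analysed but does not restore data after dropout.

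**3. Discharge model (assumed).** Progression occurs on Days 2–7, and progressors are not discharged by Day 21. Other patients' discharge times are lognormal with median 10 days and log-scale SD 0.5, the same in both arms.

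- Discharged by Day 21 among non-progressors: Φ[(ln 21 − ln 10)/0.5] = Φ(1.484) = 0.931.
- True proportion, all assigned: control 0.78 × 0.931 = 0.73; teprenone 0.90 × 0.931 = 0.84. The difference is 11 points.
- All progressors censored: both arms estimate 0.93, a difference of 0. The control shift is 0.93 − 0.73 = 0.20, about 3 standard errors, with SE = √(0.726 × 0.274/50) = 0.063.
- Half censored (early-censoring approximation): control 0.726/0.89 = 0.82; teprenone 0.838/0.95 = 0.88. The difference is about 7 points.

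Simulated log-rank power at one-sided 10%, 50 per arm, at least 1,500 trials per scenario (simulation error about 1.3 points):

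| Share of progressors leaving | Day-21 estimate, control / teprenone | Power |
|---|---|---|
| none | 0.73 / 0.84 | about 48% |
| a quarter | – | 38% and 41% in repeat runs |
| half | 0.81 / 0.88 | about 31% |
| all | 0.93 / 0.93 | about 12% |

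With all leaving, power falls from 54% to 15% at a median of 7 days and from 35% to 10% at 14 days.

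**4. A second model that allows an effect on recovery speed.** Recovery and progression have competing exponential hazards λr and λp, with λp set to give 22% and 10% progression by Day 21. True recovery by Day 21 is λr/(λr + λp) × [1 − exp(−21(λr + λp))]. With every progressor censored, the estimate is 1 − exp(−21λr). For an assumed control median of 7 days, λr = ln 2/7 = 0.099, and the control estimate is 1 − exp(−2.079) = 0.875. There were 5,000 simulated trials per row.

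| Recovery hazard ratio (assumed) | True difference | Censored difference | Rejection, kept at risk to Day 21 | Rejection, censored |
|---|---|---|---|---|
| 1.0 | 71.4% vs 80.4%: 8.9 points (unrounded rates) | 0 (87.5% in both) | 0.32 | 0.10 |
| 1.3 | 13.7 points | 5.8 points | 0.63 | 0.45 |
| 1.5 | 15.5 points | 8.1 points | 0.78 | 0.69 |

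At a hazard ratio of 1.0, the hidden difference runs from 10.5 points (median 5 days) to 5.5 points (median 14 days). Where recovery itself is faster, the censored log-rank still estimates a hazard ratio of about 1.3 or 1.5. The effect is then attenuated but not lost.

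**The case against.** The strongest reply is that censoring is inferred. The protocol names no Kaplan-Meier, log-rank or censoring rule for these three endpoints. A statistical analysis plan not shown here may handle progression properly, for example by using the recorded progression itself. That stands, and it is why the point concerns what the stated rules permit. It does not remove the point, because no later analysis can use outcomes that sections 8 and 14 allow the trial to stop collecting.

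Second, the progression criterion is discretionary and section 8 does not define dropout. The protocol plainly expects to observe some progressors: intubation is the primary endpoint, and section 5 has an assessment at intubation. That also stands, so the case in which all leave is an upper bound.

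A reader might infer that the plan erases any effect on recovery. The documents do not support that. It needs every progressor to leave and no effect on recovery speed, and the protocol states neither.

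A reader might also carry the discharge result over to fever. Only discharge was modelled with progressors as non-events. Section 6 defines fever alleviation by temperature without antipyretics, which an intubated patient can meet.

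Finally, the efficacy decision in section 8 rests on intubation, no power is claimed for these endpoints, and the modelled bias runs against teprenone. All true, and it limits the consequence. Section 11 does call "time to fever resolution" a reasonable primary endpoint, but that is a separate inconsistency and I give it no weight here.

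**Conclusion.** The point holds in a limited form. As written, the protocol permits efficacy data to stop at disease progression, and an ordinary analysis of the three recovery times would then be informatively censored. The direction is clear if the drug prevents progression: recovery is overstated in both arms, more in controls, and the benefit is attenuated.

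The size depends on assumptions the documents do not settle: the share of progressors who leave, the recovery-time distribution, and intubation rates standing in for progression. In the discharge model at a median of 10 days, half leaving costs about 17 points of power (48% − 31%) and all leaving about 36 (48% − 12%). These are secondary endpoints, so the trial's main conclusion is not at risk from this point. The wording should still be corrected, because the missing follow-up cannot be repaired at analysis.

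**What to change.** In section 8, limit the rule on using data up to dropout to patients whose outcomes truly cannot be obtained. In sections 8 and 14 (5), state that for patients discontinued without withdrawing consent, including for COVID-19 progression, discharge, death, fever and symptom status continue to be recorded to Day 21 in both arms, from the medical record. This concerns data collection only and leaves the criteria for stopping treatment as they are.

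Analyse the three times in all assigned patients in the efficacy population from these actual outcomes, by cumulative incidence with death as a competing event and no censoring at progression. Where discharge status after progression is unavailable, count the patient as not discharged by Day 21. Do not apply that scoring automatically to fever, which can resolve after progression under the section 6 definition.

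The cost is protocol and analysis-plan wording and a little more data collection. Section 16 already defines medical records as source documents, and discharge and death should be found there. The estimates will describe recovery in all assigned patients, not its speed among those who do well.

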# １０．Inclusion and exclusion criteria

（１）Inclusion criteria

　　All of the following criteria must be met.

1. Age 20 years or older on the date of obtaining consent
2. Diagnosis of COVID-19 is confirmed by PCR or antigen test.
3. Fever of 37.5 degrees or higher
4. Written consent to participate in this study.

（２）Exclusion criteria

　　Patient that fall under any of the following criteria is excluded from this study.

- - 1. Patients with a history of teprenone medication within 2 weeks prior to the planned start of treatment
    2. Patients who require ventilator management or extracorporeal membrane artificial lung (ECMO) management
    3. Patients with apparently active infectious diseases other than SARS-CoV-2 (Nontuberculous mycobacterial infection that does not require treatment or has not progressed for more than one month even with treatment can be enrolled.
    4. Pregnant or lactating patients
    5. Patients whose identity information is not available

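### A non-significant primary test is read as clinical ineffectiveness, although at the protocol's own power of 0.64 a drug with exactly the planned effect would get that verdict in about 36% of trials

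*Protocol*

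**What the plan says.** Section 8, under the main analysis and decision criteria, makes rejection of the null hypothesis of equal intubation rates the condition for calling teprenone effective. For any other result it says: "If not, it is considered invalid from a clinical medical standpoint". The paragraph on the method of the main analysis repeats the rule in nearly the same terms. The error rate is fixed in the same section: "The significance level for the entire study is set at 10% on one side". Section 8 also plans a risk ratio (treated over non-treated) with an exact 90% confidence interval, but gives neither a part in the verdict.

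Section 7 sets the target at 100 patients and assumes intubation rates of 22% without and 10% with teprenone. It reports "α = 0.1 (one-sided), the statistical power was 0.6406". The 22% comes from a national case series: "of 287 cases of COVID-19 infection as of March 9, 2020, information on invasive ventilation was available for 133 cases", and 29 of those 133 were intubated.

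Section 10 requires a confirmed diagnosis and "Fever of 37.5 degrees or higher". It excludes "Patients who require ventilator management or extracorporeal membrane artificial lung (ECMO) management".

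**The concern.** Failing to reject a null hypothesis shows that the treatment is ineffective only if the trial would very probably have detected a worthwhile effect. The protocol's own figure says that this trial would not: it misses the effect it was planned around more than one time in three. The rule nevertheless attaches a negative clinical conclusion to every such miss. A trial that was merely too small to decide would be reported as having shown that teprenone does not work, on the authority of a pre-specified criterion. The interval that would show readers how little had been excluded has no say in the verdict.

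**Working it through.** **Inputs.** Total 100 patients, rates 22% and 10%, one-sided level 10% (section 7; section 8 gives the same level). The allocation ratio is not stated; 50 per arm is assumed, in line with the balancing minimization in section 4.

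**Step 1: reproduce the stated power** (pooled-variance z-test).
- Mean rate: (0.22 + 0.10)/2 = 0.16.
- Standard error under the null: √(2 × 0.16 × 0.84 / 50) = 0.0733.
- Standard error under the alternative: √((0.22 × 0.78 + 0.10 × 0.90)/50) = 0.0723.
- Smallest significant difference: 1.2816 × 0.0733 = 0.0940.
- Power: Φ((0.12 − 0.0940)/0.0723) = Φ(0.360) = 0.6406.

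This matches section 7 exactly.

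**Step 2: chance of the negative verdict when the planned effect is true.** 1 − 0.6406 = 0.359, about 36%. Section 8 names a binomial test for two groups without saying which one. If it is a one-sided Fisher exact test, full enumeration gives power 0.553, so the figure becomes 1 − 0.553 = 0.447, about 45%.

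**Step 3: what such a trial would show.** Take 10/50 intubated without and 6/50 with teprenone.
- z = 0.08/0.0733 = 1.09, one-sided p = 0.14, so the null is not rejected.
- Risk ratio: 6/10 = 0.60.
- Standard error of the log ratio: √(1/10 − 1/50 + 1/6 − 1/50) = 0.476.
- Approximate 90% interval: 0.60 × exp(±1.645 × 0.476) = 0.27 to 1.31. This is a log-scale approximation; the protocol plans an exact interval.

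The planned ratio is 10/22 = 0.45, well inside that interval, yet section 8 would call the drug ineffective. Enumerating all outcomes at the planned rates with the same approximation, about 85% of the non-significant trials have a 90% interval that still reaches 0.45 or lower.

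**Step 4: conditional note on the control rate.** 29/133 = 21.8%; 287 − 133 = 154 cases had no ventilation data. If none of those 154 had been intubated, the rate would be 29/287 = 10.1%, the lowest value the series allows. Keeping the risk ratio at 10/22, which is an assumption, the formula of Step 1 gives:

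| Control rate | Treated rate | Power (z-test) |
|---|---|---|
| 22% | 10.0% | 0.64 |
| 15% | 6.8% | 0.51 |
| 10.1% | 4.6% | 0.41 |
| 25% | 11.4% | 0.69 |
| 30% | 13.6% | 0.76 |

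If the 12-point difference is held fixed instead, power rises as the control rate falls: 0.72 at 18% versus 6% and 0.80 at 15% versus 3%.

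**The case against.** **Wording and purpose.** The English is a translation, and the word rendered as invalid most likely means not effective. This is a phase II trial with a relaxed one-sided level and openly declared power, and a pre-set go/no-go rule is ordinary at that stage. What stands is that the 36% is disclosed and correctly computed. The defect remains: not effective is the same unsupported conclusion, and a decision not to proceed can be taken without claiming ineffectiveness.

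**The estimate is already planned.** Readers will see the risk ratio and its interval. That is true, and it narrows the fault to the absence of any role for them in the verdict.

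**Rewording recovers no power.** Also true. The 36% measures wrong verdicts, not a treatment effect that better wording would detect. The proposed criterion is modest too. With a drug of no effect, an approximate 90% interval excludes 0.45 in about 67% of trials at a 22% rate and about 37% at 10.1%. The remaining trials would be inconclusive on that question, which is what the data would support.

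**The control rate.** A reader might infer that 22% is too high and that true power is therefore below 0.64. The documents do not show this. Section 7 does not say how ill the 287 cases were or why 154 lacked data, and 10.1% needs no intubation in any of them. Excluding patients already needing ventilation may lower the rate, while requiring fever may raise it. The fall in power also depends on holding the risk ratio fixed. Adding a Fisher test to the 10.1% bound would give a still larger miss rate, but it combines an extreme bound with a test that the protocol does not name.

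**Conclusion.** The decision rule is wrong as written: it turns non-rejection into a conclusion of clinical ineffectiveness that the trial's size cannot support. At exactly the planned effect, the wrong verdict falls in about 36% of trials (pooled z-test, 50 per arm assumed), or about 45% under a one-sided Fisher test. The 36% follows from the protocol's own design figures and needs no doubt about the control rate. The power calculation itself is correct for the scenario it states. That the 22% rests on 133 of 287 cases is a caution only: power would be lower if the true rate were lower at the same risk ratio, and higher if it were higher.

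**What to change.** In section 8, replace both statements about a non-significant result with one saying that efficacy was not demonstrated. Add that the result is then interpreted from the planned risk ratio and its 90% interval, and that absence of the planned effect is concluded only if the interval lies wholly above the planned ratio of about 0.45 (10/22). The criterion for declaring efficacy can stay with the one-sided test at 10%. The interval answers the separate question of which effects remain possible.

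Optionally, section 7 could show power at one or two other control rates, with the assumption about the risk ratio stated. This is a courtesy to readers, since the single figure is correct.

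The cost is a few sentences in a protocol amendment. No patients, data or analyses are added. What is given up is the ability to call a non-significant result a negative finding without looking at the interval.
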